#### Pain Intensity

Pain intensity will be measured using Visual Analog Scale (VAS). This is a reliable measure of pain [35] consisting of a 100-mm line in which participants must mark between the left side (0, representing “no pain”) and 100 (representing “the worst pain imaginable”). This measure will be self-reported on a paper form.

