#### Physical function subscale of the Western Ontario and McMaster universities osteoarthritis index (WOMAC)

To assess physical function, the Western Ontario and McMaster Universities (WOMAC) questionnaire will be used, a self-administered instrument that addresses the impact and restrictions on quality of life, specifically for patients with lower limb OA [36]. The questionnaire has been translated into Portuguese and validated [37], consisting of 24 questions divided into three domains: pain, stiffness, and physical function. The physical function subscale contains 17 questions, and the score is made using a Likert scale, whereby each question is scored between “no dysfunction” (score = 0) to “extreme dysfunction” (score = 4). Total score ranges from 0 to 68, with higher scores indicating worse function. Self-reported answers will be registered on a paper form.

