### Sample size {14}

Sample size was based on detecting non-inferiority of telerehabilitation circuit training in comparison to the face-to-face method at 14 weeks after randomization, considering the primary outcomes pain (VAS) and disability (WOMAC function sub-scale). For change in VAS, a non-inferiority margin (NIM) of 16 mm was chosen as this is less than the minimum clinically important difference (MCID) of 17.5 mm from a 100-mm VAS for OA patients [55]. For change in WOMAC function sub-scale, a NIM of 7.5 units (11% of scored 0–68) was chosen as this is less than the MCID of 12% (8.16) of improvement from baseline in OA research [56]. Assuming standard deviations (SD) for changes from baseline of 17.9 mm and 12.12 units for pain intensity and physical function respectively [10, 25], 80% power and a one-sided 2.5% significance level, we needed 20 people per arm for change in pain intensity and 41 people per arm for change in physical function. However, considering 18% loss to follow-up, we needed 25 and 50 people per arm for change in pain intensity and physical function, respectively. Thus, a total of 100 people will be included in the trial. No adjustments for multiplicity was made. Sample size calculation was performed using the software G*Power, version 3.1.

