## Statistical methods

### Statistical methods for primary and secondary outcomes {20a}

A blinded data analyst will perform all analysis using the Statistical Package for Social Science, version 20.0 (SPSS Inc, Chicago, IL, USA). Baseline characteristics of participants will be presented using descriptive statistics. The between-group differences and 95% confidence interval (CI) for the post-treatment outcomes at 14-week and 26-week end-points will be calculated using mixed linear models using interaction terms of treatment group versus time with no covariate adjustment. Non-inferiority will be demonstrated if the lower bound of the two-sides 95% CI for between-group difference (telerehabilitation minus face-to-face) is above −16 mm in pain intensity and/ or −7.5 units for change in WOMAC physical function subscale at 14 weeks after randomization. Multiple imputation method will be used to impute missing data by using the multiple imputations function in SPSS [57], and an intention-to-treat analysis [58] (including all randomized participants) will be conducted. No adjustments for multiplicity will be made.

It is important to note that, if appropriate, a full statistical plan will be finalized prior to analysis.

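### The non-inferiority rule checks the wrong confidence limit: on scales where higher is worse, it sets no limit on how much worse telerehabilitation may be

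*Protocol article*

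**What the plan says.** **Scoring.** The Pain Intensity section describes the VAS as "consisting of a 100-mm line in which participants must mark between the left side", which is scored 0 for no pain, and "100 (representing “the worst pain imaginable". For WOMAC physical function the article states: "Total score ranges from 0 to 68, with higher scores indicating worse function". Both outcomes run from good (low) to bad (high).

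**Quantity compared.** Statistical methods {20a} plans "The between-group differences and 95% confidence interval (CI) for the post-treatment outcomes at 14-week and 26-week end-points", estimated from a mixed linear model with group-by-time terms and no covariates.

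**Decision rule.** The same section concludes non-inferiority if "the lower bound of the two-sides 95% CI for between-group difference (telerehabilitation minus face-to-face) is above −16 mm in pain intensity". For function, the corresponding lower bound is minus "7.5 units for change in WOMAC physical function subscale at 14 weeks after randomization".

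**Margins.** Sample size {14} gives the margins without a sign: "For change in VAS, a non-inferiority margin (NIM) of 16 mm was chosen" and "For change in WOMAC function sub-scale, a NIM of 7.5 units (11% of scored 0–68) was chosen".

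The article nowhere reverses either scale or says that change is to be calculated as baseline minus follow-up.

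**The concern.** The subtraction order is TR minus FtF, and high scores are bad. A positive difference therefore means TR patients ended with more pain or worse function. This is so for the 14-week score itself and for the usual change score (follow-up minus baseline).

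A non-inferiority claim has to rule out that TR is worse by the margin or more. On these scales the upper confidence limit must lie below +16 mm or +7.5 units. The written rule looks at the other end of the interval. A lower limit above −16 or −7.5 shows only that TR is not better than FtF by more than the margin.

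This is the trial's confirmatory criterion. Applied literally, it accepts a clearly inferior remote programme and can refuse the claim to one that works better.

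**Working it through.** **Inputs**, from Sample size {14}: margins M of 16 mm and 7.5 units; SDs of change of 17.9 mm and 12.12 units; one-sided 2.5% level; 80% power; 41 completers per arm (the larger of the two requirements); 18% loss to follow-up.

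**Step 1: reproduce the planned sample size.** n per arm = 2 × (1.96 + 0.8416)² × (SD/M)², at a true difference of zero.

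- VAS: 2 × 7.849 × (17.9/16)² = 19.6, so 20; 20/0.82 = 24.4, so 25.
- WOMAC function: 2 × 7.849 × (12.12/7.5)² = 41.0, so 41; 41/0.82 = 50.

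Both match the article. The formula is symmetric at a true difference of zero, so the sample size gives no clue to the direction of the rule and is unaffected by it.

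**Step 2: precision with 41 per arm.** SE = SD × √(2/41).

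- VAS: 17.9 × 0.2209 = 3.95 mm; 95% half-width 1.96 × 3.95 = 7.75 mm.
- WOMAC function: 12.12 × 0.2209 = 2.68 units; half-width 5.25 units.

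**Step 3: what the written rule accepts.** It passes whenever the observed TR minus FtF exceeds −M + 1.96 × SE.

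- VAS: −16 + 7.75 = −8.25 mm.
- WOMAC function: −7.5 + 5.25 = −2.25 units.

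There is no ceiling. Suppose the observed difference is +24 mm (TR worse). The interval is 24 ± 7.75, or 16.25 to 31.75 mm, so the whole of it lies beyond the margin on the harmful side. The lower limit is still above −16, and the rule declares non-inferiority.

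**Step 4: probability of declaring non-inferiority.** Let D be the true TR minus FtF difference (positive = TR worse).

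- Rule as written: Φ((D + M)/SE − 1.96)
- Upper limit below +M: Φ((M − D)/SE − 1.96)

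| Outcome | True D | As written | Upper-limit rule |
|---|---|---|---|
| VAS | −16 mm (TR better) | 2.5% | about 100% |
| VAS | −10 mm (TR better) | 33% | about 100% |
| VAS | 0 | 98.2% | 98.2% |
| VAS | +16 mm (TR worse) | >99.99% | 2.5% |
| VAS | +32 mm (TR worse) | about 100% | about 0% |
| WOMAC function | −7.5 units (TR better) | 2.5% | 99.99% |
| WOMAC function | 0 | 80.0% | 80.0% |
| WOMAC function | +7.5 units (TR worse) | 99.99% | 2.5% |
| WOMAC function | +15 units (TR worse) | about 100% | about 0% |

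Examples: for VAS at D = −10, (−10 + 16)/3.95 − 1.96 = −0.44 and Φ = 0.33. For function at D = +7.5, 15/2.68 − 1.96 = 3.64 and Φ = 0.9999.

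With all 50 per arm the pattern is the same; the thresholds in Step 3 become −8.98 mm and −2.75 units.

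**The case against.** The strongest defence is that the authors had improvement in mind. The abstract and the sample-size section speak of changes in pain and function. The sample-size section describes the WOMAC reference value as an improvement from baseline, and the decision sentence itself mentions change for WOMAC. If change is baseline minus follow-up, positive values are good, and a lower bound with negative margins is the correct rule. It would then have the intended 2.5% error at the margin and, with 41 per arm, 98.2% (VAS) and 80.0% (WOMAC) power at no difference. A group-by-time term is also a contrast of changes, so the reference to post-treatment outcomes does not prove that raw 14-week scores are compared. Finally, the coding of a change score could be left to the full statistical plan.

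Improvement coding is plausible as intent, and the error rates above do not apply under it. But the article never states that coding, and the pain clause of the decision rule does not mention change. A group-by-time contrast on scores as recorded still gives a positive value when TR is worse. The possible later plan does not remove the problem either. The article already fixes the limit, the subtraction order and the signed margins, and together these conflict with its own scales. It also promises that plan only if appropriate.

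**Conclusion.** The decision rule is wrong as written. On the scales the article defines, it bounds how much better TR may be and leaves unbounded how much worse. If TR is worse by the full margin, the chance of a non-inferiority claim is above 99.9% for each outcome instead of 2.5%. If TR is better by the full margin, that chance is only 2.5%.

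These figures assume the protocol's SDs of change, 41 completers per arm, a normal approximation, and scores analysed as recorded or as follow-up minus baseline. A different SD or number of completers would move the percentages but not the direction of the error. Only a sign convention that the article does not state would make the rule correct. The sample-size calculation is sound and is not affected.

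**What to change.** Correct the decision sentence in Statistical methods {20a}, and carry the same wording into any statistical analysis plan. Either of these works:

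1. Non-inferiority is shown if the upper limit of the two-sided 95% CI for TR minus FtF at 14 weeks (14-week score, or follow-up minus baseline) is below +16 mm for VAS and below +7.5 units for WOMAC function.
2. Keep the lower limit with −16 mm and −7.5 units, and state that change is baseline minus follow-up, so that positive values mean improvement. The model output must then be produced on that scale.

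The cost is one sentence. Margins, data collection and sample size do not change. Trial status reports two of three recruitment blocks complete and the last not yet started, so the correction should be made and dated before the final analysis. The direction is then not chosen with the final results in view.

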## Objectives {7}

The primary aim of this randomized controlled trial is to determine if the periodized circuit training applied via telerehabilitation is just as effective to the same training applied face-to-face for improving pain intensity and physical function at 14 weeks (primary time-point) and 26 weeks (secondary time-point), in individuals with knee OA.

Secondary aims are to compare clinical (muscle strength and pain catastrophizing) and morphological characteristics (body composition, intermuscular adipose tissue, and muscle architecture), as well effectiveness, adherence, acceptability, and treatment perspectives 14 and 26 weeks after treatment. Safety endpoint will be determined by recording the number of adverse events during the intervention period.

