### Interim analyses {21b}

There are no interim analyses planned.

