## Trial status

The protocol was registered on 31 March 2019, under the registration RBR-662hn2. The first two blocks of recruitment, allocation and analysis have already been completed. However, the final block of participants (*n* = 40) did not start yet due to the delay caused by the COVID-19 pandemic. Data recruitment began: 01 April 2019. Data when recruitment will be completed: 30 July 2021 - Version 2 (recruitment date updated - under review).

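### The non-inferiority rule joins pain and function by 'and/or', so a trial-level claim could rest on pain alone although the aim is joint; it should require both

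*Protocol article*

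**What the plan says.** **The aim.** Objectives {7} asks whether telerehabilitation is "just as effective to the same training applied face-to-face for improving pain intensity and physical function at 14 weeks". Both outcomes stand in one aim, and the section on primary outcomes names both as primary without ranking them.

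**The sample size.** Sample size {14} sizes each outcome on its own, at "80% power and a one-sided 2.5% significance level". It arrives at 20 per arm for pain and 41 per arm for WOMAC function, or 25 and 50 after 18% loss. The larger requirement, from function, gives the total of 100. On multiple outcomes it says "No adjustments for multiplicity was made".

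**The success rule.** Statistical methods {20a} treats non-inferiority as demonstrated when the lower limit of the two-sided 95% interval "is above −16 mm in pain intensity and/ or −7.5 units for change in WOMAC physical function subscale at 14 weeks after randomization". The same section repeats "No adjustments for multiplicity will be made". It adds that a full statistical plan will be finalised before analysis if appropriate.

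**Status.** Trial status reports "The first two blocks of recruitment, allocation and analysis have already been completed". Interim analyses {21b} states "There are no interim analyses planned".

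**The concern.** *And/or* covers two different decision rules. Under *and*, both outcomes must clear their margins. Each is tested at one-sided 2.5%, and no adjustment is needed because every test has to succeed. Under *or*, one success is enough, so a single declaration has two chances to be triggered and nothing in the plan limits the combined error.

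The rest of the protocol points to *and*: the aim is joint, and there is no reason to recruit 50 per arm for function if a result on pain, which needs only 25, could settle the matter. But someone who follows the rule as written could announce non-inferiority on pain while function fails. At this sample size pain is heavily overpowered, so under *or* the function outcome would hardly influence the verdict.

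**Working it through.** **Inputs, all from Sample size {14}.** Margins 16 mm and 7.5 units; SDs of change 17.9 mm and 12.12 units; one-sided 2.5%; 80% power; true difference taken as zero; 18% loss. Each margin is read as the largest acceptable loss with telerehabilitation. The correlation between the two outcomes is not given, so I assume values from 0 to 0.9.

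**1. Reproduce the plan's figures.** n per arm = 2 × [SD × (1.960 + 0.842) / margin]².
- Pain: 19.65, rounded up to 20. After loss: 20 / 0.82 = 24.4, so 25.
- Function: 40.99, rounded up to 41. After loss: 41 / 0.82 = 50.

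Both agree with the protocol, so the fault is in the decision rule and not in these numbers.

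**2. Power of each outcome at 41 evaluable per arm.** Power = Φ(margin / SE − 1.960), with SE = SD × √(2/41).
- Pain: SE = 3.953; 16 / 3.953 = 4.047; Φ(2.087) = 98.2%.
- Function: SE = 2.677; 7.5 / 2.677 = 2.802; Φ(0.842) = 80.0%.

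**3. Error of the *or* rule, both outcomes truly at their margins.** P(at least one passes) = 0.025 + 0.025 − P(both pass). With independent outcomes this is 0.05 − 0.025² = 0.0494. The other values use the bivariate normal distribution.

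| Assumed correlation | False claim under *or* | Joint power under *and* |
|---|---|---|
| 0 | 4.94% | 78.5% |
| 0.5 | 4.54% | 79.4% |
| 0.7 | 4.17% | 79.8% |
| 0.9 | 3.52% | 80.0% |

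**4. *Or* rule, pain truly equal and function truly 7.5 units worse.** The claim succeeds whenever pain passes, so its probability is at least 98.2%. Function can add at most the cases in which pain fails and function passes by chance; with independent outcomes that is 0.0184 × 0.025 = 0.0005. The answer therefore stays at about 98.2% whatever the correlation, and also if function is worse by more than 7.5 units. Under *and*, the same truth yields a claim at most 2.5% of the time.

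**5. Power of the *and* rule.** With independent outcomes, 0.9816 × 0.8001 = 0.785; the other values are in the table. Joint power cannot exceed the 80.0% for function alone, so the loss is at most about 1.5 points. Reaching a full 80% takes 43 evaluable per arm at correlation 0 and 42 at 0.5 or 0.8. That is 43 / 0.82 = 52.4, so 53 randomised per arm, or 42 / 0.82 = 51.2, so 52: a total of 104 to 106 against 100.

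**The case against.** **The benign reading of *and/or*.** Each outcome has its own margin and its own sample size, so the phrase could mean that non-inferiority is concluded for pain, for function or for both, each labelled. On that reading 2.5% holds for every claim, and step 4 describes a correct claim on pain beside a failed one on function. The text does not exclude this. It does not say it either: the rule is written as one declaration, and one outcome alone would not meet the joint aim. The wording needs settling on any reading.

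**The stated 2.5%.** A reader might infer that the *or* rule contradicts the plan's own significance level. It does not. Sample size {14} gives 2.5% as the level of each outcome's calculation, never as a trial-wide rate, and the lack of adjustment is disclosed twice. The 3.5% to 4.9% applies to a single overall claim with both outcomes exactly at their margins, under assumed correlations.

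**The completed analysis.** Implementation {16c} plans blocks of 20, 40 and 40 participants, so the first two hold 60 of the 100. A reader might infer from Trial status that outcomes of these 60 have been compared by arm and that the rule could be chosen with results known. The protocol does not support that. Analysis may mean assessments or the manual processing of CT and ultrasound images by blinded evaluators, no interim analysis is planned, and the data analyst is blinded. What remains is an unclear pair of statements that the sponsor should clarify. It adds nothing to the error figures.

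**Other remedies.** A fixed sequence, a Holm procedure or two labelled claims would also resolve the ambiguity. That is true; *and* is preferred because it matches the stated aim.

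**Conclusion.** The point holds for the decision rule. As written, it allows one overall non-inferiority claim to rest on either primary outcome, without multiplicity control, under a joint aim and with a sample size set by function. Read as *or*, the one-sided error of that claim is about 3.5% to 4.9% for assumed correlations of 0.9 down to 0.

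The more serious consequence is the roughly 98% chance of success with pain equal and function at its margin. It depends on the protocol's SDs and 41 evaluable per arm, and hardly at all on the correlation. The documents show no breach of the per-outcome 2.5% and no use of results by arm.

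**What to change.** 1. In Statistical methods {20a}, replace *and/or* with *and*: overall non-inferiority is claimed only if both outcomes meet their margins at 14 weeks, each at one-sided 2.5%. The statement that no multiplicity adjustment is made is then justified.
2. State that a result on one outcome alone will be reported as specific to that outcome and not as the trial's conclusion.
3. Fix this rule before any comparison by arm, in a protocol amendment or in the statistical plan.
4. In Sample size {14}, restate power as about 78.5% to 80% for the joint claim at 41 evaluable per arm.
5. Separately, clarify whether the analysis reported under Trial status included any comparison by arm. If it did, disclose it and reconcile it with Interim analyses {21b}; if it did not, correct the wording.

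**Cost.** At the planned 100 participants, at most about 1.5 points of power; a full 80% would need 104 to 106. Keeping *or* with a Bonferroni split (one-sided 1.25% each) would cost more: 80% power for function would need 50 evaluable and 61 randomised per arm, and at the planned 41 evaluable its power would fall to 71.2%.

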### Interim analyses {21b}

There are no interim analyses planned.

### Methods for additional analyses (e.g., subgroup analyses) {20b}

There are no subgroup analyses planned.

### Methods in analysis to handle protocol non-adherence and any statistical methods to handle missing data {20c}

The primary and secondary outcomes will be assessed using an intention-to-treat-analysis. Multiple imputation method will be used to impute missing data.

### Plans to give access to the full protocol, participant-level data, and statistical code {31c}

The full protocol, participant-level data, and statistical code can be made available by the Trial Coordinator upon reasonable request.

## Oversight and monitoring

### Composition of the coordinating center and trial steering committee {5d}

The coordinating center is located at the Department of Physical Therapy at the Federal University of São Carlos and comprises the Trial Coordinator, the principal investigator, the radiologist doctor, the radiologist technician, 5 physical therapists, 2 computer scientists, and the data analysts. The study team meets weekly. There is no trial steering committee or public involvement group.

### Composition of the data monitoring committee, its role, and reporting structure {21a}

A data monitoring committee was not considered as this study adopts a low-risk intervention, and an interim analysis is not planned in this study.

### Adverse event reporting and harms {22}

Participants who experience any adverse event are instructed to report these to their physical therapist. All adverse events reported by the participant or observed by the physical therapist during sessions will be recorded. In this RCT, adverse events are defined as any problem experienced during the execution of the study as a result of the assessments, exercise protocol, and/or advice given by the physical therapist.

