#### Intervention description {11a}

##### Face-to-face (FtF) circuit protocol

Participants allocated to this group will attend all of their exercise sessions supervised by a trained physical therapist in the Federal University of São Carlos (UFSCar).

The exercise protocol will be performed in a group of up to 5 participants, three times a week, for 14 weeks, totaling 42 sessions [7]. Each session will consist of 5 min of warm-up (stationary bike or walk), circuit protocol, and 5 min of stretching exercises (cool down). Immediately after the warm-up, participants will begin the circuit protocol consisting of exercises for the upper limbs, lower limbs, trunk, and global exercises.

Participants will be instructed to perform each exercise as fast as possible, with the maximum number of repetitions during the time set for the training phase (light, moderate, or intense), in order to ensure the aerobic component [7]. After the first exercise, the participant should move to another station, following a specific order and allowing different muscle groups to alternate between rest and work, favoring recovery and minimizing the risk of muscle fatigue [7].

During the first week of exercise, participants will be familiarized with the equipment and exercises that will be performed during the protocol, performing stratified light exercises, where each exercise should be performed for only 10 s [7]. In the second, third and fifth weeks of training, participants will also perform exercises stratified as light, but each exercise will last 20 s. Moderate exercises will be performed in the sixth, eighth, and ninth weeks, lasting 30 s each. Intense exercises will be performed in the eleventh, twelfth, and fourteenth weeks, lasting 40 s each. The fourth, seventh, tenth, and thirteenth weeks will be considered as regenerative weeks, during which light exercises will be performed for a shorter time (10 s). For all intensities, a maximum transition interval of 30 s between stations will be implemented [7].

The exercises that compound each of the circuit training phases, as well as the execution time are presented in Additional file 1.

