The TR group will also receive periodic phone calls from a single previously trained researcher/physical therapist. The phone calls will take place in weeks 2, 3, 4, 6, 8, 11, and 14; they will be recorded and will last approximately 20 min. In addition, it should be noted that phone calls will be made at participant’s preferred timed and will be motivating and instructive; however, participants will not be informed when calls will be performed. During these phone calls, a semi-structured interview will be performed, as proposed by Hinman et al. [32]. Table 1 presents the semi-structured interview guide. In addition, during these calls, it will be possible to detect possible difficulties with carrying out the exercises, as well as monitor the progress in subsequent calls, assessing the ability to perform the exercises, changes in symptoms, and functional capacity.

**Table 1 Tab1:** Semi-structured interview guide

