**Questions**	
1. How was your week?	
2. How are you feeling?	
3. Are you having difficulty performing the exercises?	
4. How often have you been doing the exercises and at what time?	
5. Is any family member doing the exercises with you?	
6. Is there something in your routine that you could modify to be able to perform the exercises?	
7. Do you think exercise is beneficial to your health?	

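### Adverse events are ascertained differently in the two arms, so the safety count is likely to under-count telerehabilitation events and is not comparable between arms

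*Protocol article*

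**What the plan says.** The Objectives section of the protocol article sets a safety endpoint: "Safety endpoint will be determined by recording the number of adverse events during the intervention period".

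The section on adverse event reporting and harms gives two routes into that count. The first is spontaneous report: "Participants who experience any adverse event are instructed to report these to their physical therapist". The second is therapist observation: "All adverse events reported by the participant or observed by the physical therapist during sessions will be recorded". It defines an adverse event as "any problem experienced during the execution of the study as a result of the assessments, exercise protocol, and/or advice given by the physical therapist".

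The intervention descriptions fix how much therapist contact each arm has:

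- **FtF:** participants "will attend all of their exercise sessions supervised by a trained physical therapist", in groups of up to five, "three times a week, for 14 weeks, totaling 42 sessions".
- **TR:** the same programme is done remotely, after one individual visit before the start. "The phone calls will take place in weeks 2, 3, 4, 6, 8, 11, and 14". Each call is recorded and lasts about 20 minutes.

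Table 1 prints the seven questions of the call guide. The two nearest to harms are an open question on how the participant feels and "Are you having difficulty performing the exercises". The text around the table adds that the calls will pick up difficulties and follow changes in symptoms. The TR diary is described as a record of exercise days.

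**The concern.** Of the two routes, therapist observation during sessions exists in one arm only. The other, participant report, depends on the participant noticing a problem, linking it to the trial and mentioning it. FtF participants meet a therapist at every session. TR participants have a scheduled conversation in half of the weeks and are not asked directly about injuries, falls or adverse events. A count built this way mixes how often harm occurs with how often it is seen.

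The trial asks whether remote delivery can stand in for supervised delivery, and harm that nobody observes is the obvious safety question about unsupervised exercise. Event counts by arm are likely to be read beside any non-inferiority conclusion. A lower TR count could then pass for reassurance when it partly reflects weaker ascertainment. The Discussion concedes that TR exercise participation is self-reported but makes no such reservation about harms.

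**Working it through.** **1. Contacts at which an event can come to light (planned maximum).**

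- FtF: 3 sessions per week × 14 weeks = 42, which reproduces the protocol's own figure. All are supervised.
- TR: calls in weeks 2, 3, 4, 6, 8, 11 and 14 = 7. None involves watching an exercise session.
- Ratio of contacts: 42 / 7 = 6. This is a ratio of contacts, not of detection.
- Weeks without a TR call: 1, 5, 7, 9, 10, 12 and 13, so 7 of 14. The longest gap between calls is 3 weeks (8 to 11, and 11 to 14).

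**2. Routes side by side.**

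| Route | FtF | TR |
|---|---|---|
| Therapist observes the session | 42 sessions | none |
| Instruction to report spontaneously | yes | yes |
| Scheduled one-to-one enquiry with open prompts | none described | up to 7 calls |
| Explicit harm question, same in both arms | none described | none in the guide |

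**3. What unequal capture does to a count.** Let *n* be the participants per arm, *p* the true risk of an event per participant and *c* the probability that an event is captured.

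- Expected recorded count = *n* × *p* × *c*.
- With equal true risks, recorded TR/FtF ratio = *c*(TR) / *c*(FtF).
- The true TR/FtF risk ratio that would look like 1 is the inverse, *c*(FtF) / *c*(TR).

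The protocol gives *n* = 50 per arm (100 participants, 1:1). It gives neither *p* nor *c*, so everything below is assumed: *p* = 20%, *c*(FtF) = 0.9 to 1.0, *c*(TR) = 0.4 to 0.8.

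- FtF: 50 × 0.20 × 0.9 = 9, up to 50 × 0.20 × 1.0 = 10.
- TR: 50 × 0.20 × 0.4 = 4, up to 50 × 0.20 × 0.8 = 8.
- Recorded ratio: 0.4 / 1.0 = 0.40, up to 0.8 / 0.9 = 0.89.
- True risk ratio that would look equal: 0.9 / 0.8 = 1.125, up to 1.0 / 0.4 = 2.5.

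On the percentage scale, with *p* = 30%, *c*(FtF) = 0.9 and *c*(TR) = 0.5, the arms would show 0.30 × 0.9 = 27% and 0.30 × 0.5 = 15%. With *c*(TR) from 0.4 to 0.7, TR would show 12% to 21%.

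**4. Sensitivity to the assumption.** If the call prompts raised TR capture to the FtF level, the ratio would be 0.9 / 0.9 = 1.00. If TR capture were complete and FtF capture 0.9, it would be 1.0 / 0.9 = 1.11. The direction therefore depends on capture rates that the protocol does not supply. With one common method giving the same capture in both arms, the ratio is 1.00 whenever true risks are equal.

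**The case against.** The strongest reply is that TR is not left unasked. The calls are one-to-one and recorded, and they include open prompts and attention to changes in symptoms. The individual visit before the start covers warning signs for interrupting a session, and participants in both arms are told to report events. No scripted enquiry is described for FtF, which runs in groups. On this view the contrast is passive observation against prompted enquiry, and the 6:1 contact ratio says little about detection. This stands as far as it goes: it may narrow the gap, and it rules out certainty about direction. It does not make the two methods alike, and a comparison of counts needs like methods.

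A reader might infer that the count must favour TR by design, or that it will be lower in TR even when true harm is equal or greater. The documents do not support either. They give no capture rates, and a large enough excess risk in TR would outweigh weaker capture. Nor does the causal wording in the adverse event definition single out TR, since it applies to both arms.

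It can also be said that no between-arm safety test is planned and that elicitation scripts often sit in a fuller document. Both are fair. But the article does state the recording rule and does print the call guide. Followed exactly, they yield counts that cannot be compared, whether or not a test is done.

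**Conclusion.** The point holds for the safety endpoint. Ascertainment differs by arm, is likely to under-count TR events, and makes the adverse event counts non-comparable. That rests on stated facts: one capture route is available at 42 supervised sessions in FtF and at none in TR, while TR has up to 7 calls with open prompts and no explicit harm question.

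The size of the bias, and certainty about its direction, cannot be derived from the documents. The 0.40 to 0.89 range and the 27% against 15% example rest wholly on assumed risks and capture probabilities that set TR below FtF, and they serve as illustration only. The non-inferiority analysis and the sample size do not depend on this. The change should be made because it is cheap and the last block can still benefit.

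**What to change.** For the remaining block (n = 40, not started according to Trial status):

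- Ask one identical harm question in both arms in weeks 2, 3, 4, 6, 8, 11 and 14: at the existing calls in TR and at a session in FtF. For example: since we last asked, have you had any injury, fall, new pain or other problem?
- Repeat it at the 14-week assessment, collected by someone other than the blinded assessor or on a separate self-completed form, so that answers do not reveal the arm.
- Record every event first, and relatedness to trial procedures as a separate item.
- Base any between-arm comparison on events elicited by this common question. Still report all session-observed and spontaneously reported events, by arm and source.
- State that counts for the first 60 participants (20 + 40 in the first two stages) are not comparable between arms.

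**Cost.** One question at existing contacts, and one short form or a second person at 14 weeks. Ascertainment changes between blocks, so the blocks should not be pooled for this comparison. The common-method comparison covers only about 20 per arm; at the assumed 20% risk and full capture that is 20 × 0.20 = 4 expected events per arm, enough for description only. Recorded counts will rise, partly through the post-exercise muscle soreness that the consent information already lists as a risk.
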